### Data management {19}

All the obtained data will be stored in the data centre of the Sklifosovsky Research Institute for Emergency Medicine. These data will be unavailable to all parties until the final analysis.

### Confidentiality {27}

Each patient will be assigned a unique number; only the investigator team has access to the ID of the recruited participants.

### Plans for collection, laboratory evaluation, and storage of biological specimens for genetic or molecular analysis in this trial/future use {33}

Not applicable; no biological sampling nor laboratory investigation is planned for this study.

## Statistical methods

### Statistical methods for primary and secondary outcomes {20a}

The results will be analysed using the intention-to-treat principle. Statistical significance will be defined as *p* < 0.05 based on a two-sided test. No adjustments for multiple tests are planned. The normality of variables will be evaluated using the Shapiro-Wilk statistic. Student’s *t*-test (for normally distributed data) and Pearson’s chi-square test (for categorical data) will be used to reveal differences in symptom rates among the groups. Multiple linear regression will be used to measure point estimates and confidence intervals for group differences in the ODI and clinical scale scores from baseline to the 2-year follow-up.

The non-parametric Mann-Whitney *U* test will be used to reveal differences in continuous variables between groups both pre- and postoperatively. Continuous data within the groups will be compared using the Wilcoxon test. Categorical parameters among the groups will be compared using Fisher’s exact two-tailed test.

Complication incidence during the 2-year follow-up will be compared between groups using Kaplan–Meier survival curves and the log-rank test. The significance of the risk factors (predictors) for all registered complications will be evaluated using univariate and multivariate logistic regression models.

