## Introduction

### Background and rationale {6a}

Degenerative lumbar disease is one of the most common chronic diseases worldwide. The general incidence of lumbar stenosis accompanied by a significant deterioration in the quality of life reaches 5% among patients aged < 50 years and approximately 10–15% among elderly patients (50–70 years old). Moreover, lumbar stenosis appears to be one of the most common causes of decompression and fusion interventions in the lumbar spine in 50+ years old patients [1]. Applicable surgery includes the removal of bone and ligamentous structures compressing the cauda equina roots inside the spinal canal. The necessity for significant facet joint resection results in instability of the corresponding spinal segment and/or kyphotic deformation, leading to an obligatory subsequent interbody fusion.

One of the most controversial and unresolved problems of current degenerative spine management is the necessity of spinal segment fusion in patients with grade C and D lumbar stenosis according to the Schizas classification [2] without any radiological signs of instability. The decompression alone method is associated with significantly lower 2-year payments when treating stenosis [3]. Furthermore, the meta-analysis conducted by Ma et al. [4] reported a lower number of complications in the decompression-only patients’ group, while the fusion method demonstrated greater clinical improvement. According to the meta-analysis conducted by Shen et al. [5], the decompression method was associated with a shorter hospital stay, but a greater shift in the mean difference value for clinical improvement was observed in favour of the fusion group. It is important to note that both of these meta-analyses had limitations due to the inclusion of patients with lumbar spondylolisthesis, which could have a significant impact on the clinical outcomes.

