### Trial design {8}

This study is an open-label, non-inferior, multicentre, randomized controlled trial. All enrolled subjects will be divided into two concurrent groups based on the surgical technique applied (decompression or decompression with fusion).

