## Methods: participants, interventions, and outcomes

### Study setting {9}

This study involves five surgeons from three independent centres performing surgery on patients with degenerative spines. These included Sklifosovsky Research Institute for Emergency Medicine and Federal Center for Brain and Neurotechnologies as major centres and Pirogov’s National Medical and Surgical Center as a level 3 trauma centre. All participating spine surgeons are highly experienced (more than 12 years) in surgery for degenerative spine diseases and perform at least 180 operations annually. Both surgical techniques (decompression and decompression with fusion) have been used in all three clinical centres for more than 10 years. Fusion is routinely used in cases of instability that are confirmed radiologically or intraoperatively. The decompression technique was selected based on the surgeon’s personal opinion. However, all surgeons are highly experienced in both types of surgery.

In all cases, rehabilitation treatment is to be carried out by Branch No. 3 of the Moscow Scientific and Practical Center for Medical Rehabilitation, Restorative and Sports Medicine. Three experienced rehabilitation specialists will participate in the study. To avoid postoperative treatment heterogeneity, they will use a unified protocol for the postoperative treatment of all patients in the study

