#### Sample size {14}

Following a non-inferiority study design, we calculated the sample size based on the primary outcome. According to the most recent randomized trial [6], the standard deviation for the ODI in the fusion group is 20 points. With a non-inferiority margin of δ = 12, two-sided α-level of 0.05, power of 80%, and 1:1 allocation ratio, the required sample size is 70 patients. Considering the potential of 20% of patients missing the obligatory follow-up procedures, we plan to include at least 86 patients (43 patients per group).

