### Interim analyses {21b}

Interim analysis of the obtained follow-up data will be available by 12 months postoperatively for at least 20 patients in each cohort. The criteria for study termination include the following: (1) the number of repeated surgeries in any group exceeds 50%, (2) any group demonstrates a higher frequency of negative neurological postoperative outcomes and/or significant decline of ODI level compared to baseline by at least 10 points, and (3) the number of postoperative complications exceeding 50% in any group.

An interim analysis will be performed by an investigator not involved in patient treatment ([name], MD, PhD).

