### Methods for additional analyses (e.g., subgroup analyses) {20b}

No additional analyses are planned.

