### Methods in analysis to handle protocol non-adherence and any statistical methods to handle missing data {20c}

For missing outcome data, multiple imputations will be used.

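### Non-inferiority rests on intention-to-treat alone, although intraoperative conversion to fusion is left open and would be expected to favour the claim

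*Protocol article*

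**What the plan says.** Protocol article, Trial design {8}: "This study is an open-label, non-inferior, multicentre, randomized controlled trial". Sample size {14} sets the margin: "With a non-inferiority margin of δ = 12" on the ODI.

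Three items fix the analysis:

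- Statistical methods {20a}: "The results will be analysed using the intention-to-treat principle". No other analysis population is named.
- Additional analyses {20b}: "No additional analyses are planned".
- Protocol non-adherence and missing data {20c}: "For missing outcome data, multiple imputations will be used". This is the item's whole content.

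On the route to conversion, Study setting {9} says of the participating centres: "Fusion is routinely used in cases of instability that are confirmed radiologically or intraoperatively". Table 1 (Eligibility criteria {10}) excludes instability on functional radiography and spondylolisthesis above 3 mm. It cannot exclude instability first found at operation. Item {11b} on discontinuing or modifying allocated interventions covers withdrawal from the trial, not a change of operation. Table 2 schedules collection of surgery data during the inpatient stay, and of complications and repeat operations up to 24 months.

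**The concern.** In a superiority trial, patients who receive the other arm's treatment usually shrink the observed difference and make the claim harder to reach. In a non-inferiority trial the same shrinkage makes the claim easier to reach. A patient allocated to decompression but fused at the index operation has an observed 24-month ODI, so multiple imputation does not touch the case. Under intention-to-treat that value counts as a decompression result.

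The Discussion hopes the trial will help surgeons avoid fusing such patients as a precaution. If part of the decompression arm had in fact been fused, and no planned analysis showed how much the result depended on those patients, that conclusion would be hard to defend. A per-protocol definition chosen after the data are seen would carry little weight.

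**Working it through.** **Inputs from Sample size {14}.** Margin 12 ODI points, SD 20, two-sided alpha 0.05, power 80%, 1:1 allocation, 70 evaluable patients (35 per group), 86 planned (43 per group).

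**The plan's own figure.** n per group = 2 × SD² × (z_alpha + z_power)² / margin².

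- At two-sided 0.05 (one-sided 0.025): 2 × 400 × (1.960 + 0.842)² / 144 = 43.6, so 44 per group and 88 in total.
- At one-sided 0.05: 2 × 400 × (1.645 + 0.842)² / 144 = 34.4, so 35 per group and 70 in total.

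The stated 70 therefore matches one-sided 0.05, not the stated two-sided 0.05. That mismatch is a separate matter. Here it only means that the effect of conversion is shown at both levels.

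**Dilution.** Let D be the true ODI deficit of decompression without conversion, and c the share of the decompression arm converted at the index operation. If converted patients reach the fusion-arm mean and are otherwise typical of their arm, intention-to-treat estimates D(1 − c). With D at the margin:

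P(declare non-inferiority) = Φ( [12 − 12(1 − c)] / SE − z ), with SE = 20 × √(2/n).

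For n = 35, SE = 4.78. Worked at c = 10%: (12 − 10.8)/4.78 − 1.96 = 0.25 − 1.96 = −1.71, and Φ(−1.71) = 4.4%. At c = 25%: 3/4.78 − 1.96 = −1.33, giving 9.1%.

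| Converted (assumed) | Intention-to-treat difference | 35 per group, one-sided 0.025 | 43 per group, one-sided 0.025 | 35 per group, one-sided 0.05 |
|---|---|---|---|---|
| 0% | 12.0 | 2.5% | 2.5% | 5.0% |
| 5% | 11.4 | 3.3% | 3.4% | 6.4% |
| 10% | 10.8 | 4.4% | 4.6% | 8.2% |
| 15% | 10.2 | 5.7% | 6.2% | 10.2% |
| 20% | 9.6 | 7.2% | 8.0% | 12.7% |

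The protocol gives no conversion rate, so every value of c is an assumption.

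**Should the per-protocol set also drop later fusions?** Those are decompression patients whose first operation did not suffice. Suppose the excluded share c would have been 10 points worse than the arm mean (an assumption). The remaining patients then look better by 10c/(1 − c). At c = 10% that is 1.11 points, with SE = 20 × √(1/31.5 + 1/35) = 4.91. The false-declaration rate is Φ(1.11/4.91 − 1.96) = 4.1%. At 15% and 25% it is 5.4% and 9.4%. Dropping later fusions would thus bring in a bias of about the size that the analysis is meant to detect.

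**Precision of the supportive analysis.** With a true difference of 0, 35 per group and one-sided 0.025, power with everyone included is 70.9%. With 10% or 20% of the decompression arm removed for conversion it is 68.5% or 65.8%.

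**The case against.** **Conversion may be rare.** The sentence in Study setting {9} describes the centres' practice, not a trial procedure. Radiographic instability is excluded, and the decompression technique in {11a} must preserve part of the facet joints. The Background does say "The necessity for significant facet joint resection results in instability of the corresponding spinal segment", but that concerns extensive resection, which the technique is meant to avoid. This stands as far as frequency goes. A reader might infer that the protocol expects frequent conversion, but it does not say so. It leaves the intraoperative route open and plans nothing for it.

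**Repeat surgery is not forecast.** A reader might infer from Table 2, or from the stopping criterion in {21b}, "the number of repeated surgeries in any group exceeds 50" per cent, that later fusion in the decompression arm is expected. Table 2 only lists a data item and {21b} only sets a threshold. Neither says that the repeat operation is a fusion or in which arm it occurs. This stands.

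**Intention-to-treat is a legitimate answer.** For a choice between two surgical strategies, later rescue fusion is part of the outcome of decompressing first, and keeping it in its arm is a treatment-policy estimate. This stands for later fusion, so the point is limited to conversion at the index operation. Intention-to-treat is right as the primary analysis; the weakness is having nothing beside it.

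**The direction is not certain.** Converted patients may do worse than planned fusions, which would offset the dilution. This stands.

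**An article condenses.** The heading of {20b} offers subgroup analyses as its example, and supportive analysis sets are often left to a fuller document. This stands only in part. The sentence in {20b} is a general negative, and the item headed non-adherence is filled with something else. An analysis plan that added a per-protocol set would depart from {20b} as written.

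**Conclusion.** The point holds for conversion at the index operation. The protocol fixes intention-to-treat as the sole basis of a non-inferiority claim, rules out further analyses and leaves non-adherence unaddressed, while its own text leaves conversion to fusion possible. If 10% to 25% of the decompression arm were converted and did as well as the fusion arm, with a true deficit of 12, SD 20 and 35 per group, the false non-inferiority rate would be about 4.4% to 9.1% against a nominal 2.5%. The conversion rates and the outcome of converted patients are assumptions. Bias towards non-inferiority is the expected direction, not an established one.

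A reader might go further and require non-inferiority in a second, co-primary set that also excludes later fusions. The material does not support that. Such exclusions remove decompression failures after randomisation, and requiring both sets would not restore the 2.5% level. The change should be made, but it does not call the primary analysis into question.

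**What to change.** Keep intention-to-treat as the primary analysis. Amend {20b} and {20c} to:

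1. Prespecify a supportive per-protocol analysis with the same model and the same 12-point margin, restricted to patients who received their allocated index operation.
2. Report intraoperative conversions and later index-level fusions by arm.
3. State that a non-inferiority claim will be described as robust only if the two analyses agree.
4. Keep patients with later fusion in their allocated arm in both analyses, and examine them only in a sensitivity analysis, for example one that assigns them an unfavourable ODI.

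Settle these definitions before any outcome data by arm are examined.

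The cost is one or two more model runs on data that Table 2 already schedules. The per-protocol set is smaller and not fully protected by randomisation. Conversion depends on what is found at operation, so that set can be selected too. This is why it accompanies intention-to-treat and does not replace it.

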**Methods:**

This study is focused on the non-inferior clinical results of decompression compared with the standard fusion procedure. In the decompression group, the spinous process, the interspinous and supraspinous ligaments, part of the facet joints, and corresponding parts of the vertebral arch are to be preserved intact. In the fusion group, decompression is to be supplemented with transforaminal interbody fusion. Participants meeting the inclusion criteria will be randomly divided into two equal groups (1:1), depending on the surgical method. The final analysis will include 86 patients (43 per group). The primary endpoint is Oswestry Disability Index dynamics at the end of the 24-month follow-up compared to the baseline level. Secondary outcomes included those estimated using the SF-36 scale, EQ-5D-5L, and psychological scales. Additional parameters will include sagittal balance of the spine, fusion results, total cost of surgery, and hospital stay followed by two-year treatment. Follow-up examinations will be performed at 3, 6, 12, and 24 months

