## Outcomes {12}

### Primary endpoint

The primary endpoint includes the dynamics of ODI parameters at the end of the 24-month follow-up compared to the baseline level [7]. This patient-reported measurement precisely estimates the impairment of a participant’s quality of life resulting from low back pain and clearly reflects the clinical outcome of the treatment. Parameter assessment is to be considered at all stages of the study beginning from baseline examination, followed by a follow-up examination 2 years postoperatively. The questionnaire consists of 10 sections, comprising six statements per section. Each answer is assessed using six grades (ranging from 0 to 5) with a maximum score of 50 points per participant. Subsequently, the total score is converted into a percentage ratio (from 0 to 100%). If any of the sections are not applicable or have been withdrawn for ethical reasons, the total score is calculated within nine sections and is divided by 45.

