## Discussion

Currently, the selection of surgical solutions for lumbar stenosis remains controversial. This study was designed to provide surgeons with high-level evidence by comparing the clinical outcomes of the two most popular treatment methods. The non-inferiority study design [14] was chosen because according to the current evidence [4, 5] and our experience, both methods are non-inferior (comparable) in terms of the primary endpoint, while there may be superiority in certain secondary endpoints, such as cost effectiveness and lower complication rates.

The non-inferior margin was chosen based on the minimum clinically important difference (MCID), which represents the smallest improvement considered worthwhile by a patient. For patients with lumbar spine stenosis, the MCID in ODI score ranges from 12.54 to 12.8 points [15, 16]. Therefore, a non-inferiority margin of *δ* = 12 was selected according to this data.

To develop the structure of this study, we did our best to maximise the homogeneity of the participant groups. For this purpose, we used precise inclusion and exclusion criteria and accurately restricted the range of surgical methods and postoperative rehabilitation treatment. The key role of postoperative rehabilitation in favourable clinical outcomes is widely known. In our study, all included participants are scheduled for rehabilitation treatment at the same rehabilitation centre within 3 months postoperatively. We believe that these conditions maximise the homogeneity of the participant groups and limit possible clinical outcomes by several factors. We suggest that the mentioned structure of the study implicates decompressive intervention as the only factor for favourable clinical outcomes compared to spinal fusion.

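### The only stated decision rule, two-sided p<0.05, tests equality; the planned ODI confidence interval has no stated level and is not compared with the 12-point margin

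*Protocol article*

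**What the plan says.** The design is unambiguous. Trial design {8} states: "This study is an open-label, non-inferior, multicentre, randomized controlled trial". The Abstract (Methods) gives the direction: "This study is focused on the non-inferior clinical results of decompression compared with the standard fusion procedure". The primary outcome is ODI change over two years: "The primary endpoint includes the dynamics of ODI parameters at the end of the 24-month follow-up compared to the baseline level".

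The margin appears in two places. Sample size {14} uses it: "With a non-inferiority margin of δ = 12, two-sided α-level of 0.05, power of 80%, and 1:1 allocation ratio, the required sample size is 70 patients". The Discussion gives its basis: "The non-inferior margin was chosen based on the minimum clinically important difference (MCID").

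Statistical methods for primary and secondary outcomes {20a} does not mention the margin. It sets one general criterion, "Statistical significance will be defined as *p* < 0.05 based on a two-sided test", and lists tests for between-group differences. Among these is the Mann-Whitney U test, assigned to continuous variables before and after surgery with no exception for ODI. The same section also says: "Multiple linear regression will be used to measure point estimates and confidence intervals for group differences in the ODI and clinical scale scores". It gives no confidence level and no limit against which the interval will be read. The sections on interim analyses {21b}, additional analyses {20b} and missing data {20c} supply no other rule for the primary conclusion.

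**The concern.** A non-inferiority trial must reject the hypothesis that decompression is worse than fusion by 12 points or more. A two-sided p<0.05 criterion rejects the hypothesis that the two are equal. These are different questions, and a trial of this size can easily fail to reject equality while leaving a disadvantage of more than 12 points plausible. The criterion stands in the section that covers the primary outcome and is not limited to the others, so it is a stated rule that does not fit the design, not merely an omitted detail.

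The Mann-Whitney wording adds to the problem. ODI is a continuous variable, so as written it is covered, and a rank-test p value cannot be set against a margin of 12 points.

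The planned regression interval could settle the matter, but its level is open. Leaving the level open until the data are in allows a choice between a 95% and a 90% interval, which differ in how large an observed disadvantage they tolerate. The trial's main claim, that surgeons may choose the less invasive operation, depends on this rule.

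**Working it through.** Inputs from Sample size {14}: margin 12; two-sided alpha 0.05; power 80%; 1:1 allocation; 70 evaluable (35 per arm); 86 enrolled (43 per arm); and "the standard deviation for the ODI in the fusion group is 20 points". Assumption: true difference 0. The article states none, and the Discussion treats the methods as comparable. Differences are decompression minus fusion, so positive means decompression is worse.

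**1. Reproducing the plan's 70.** n per arm = 2 × [SD × (z(1−a) + z(0.80)) / margin]², with a the one-sided alpha.
- a = 0.025 (the alpha as written, a 95% interval): 2 × [20 × (1.960 + 0.842)/12]² = 43.6, so 44 per arm, 88 in total.
- a = 0.05 (a 90% interval): 2 × [20 × (1.645 + 0.842)/12]² = 34.3, so 35 per arm, 70 in total.

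The plan's 70 therefore matches one-sided 0.05, not the two-sided 0.05 written beside it. The interval level cannot be inferred safely from this section.

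**2. Power under each interval level.** SE = 20 × √(2/n): 4.78 at 35 per arm and 4.31 at 43. Power = Φ(12/SE − z).

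| Per arm | 12/SE | 95% interval (z = 1.960) | 90% interval (z = 1.645) |
|---|---|---|---|
| 35 | 2.51 | 71% | 81% |
| 43 | 2.78 | 79% | 87% |

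With the t distribution, the figures at 35 per arm are 70% and 80%.

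**3. What the two rules conclude at 35 per arm.** t(0.975, 68 df) = 1.995, so the 95% half-width is 1.995 × 4.78 = 9.54.
- The difference test is not significant for an observed disadvantage up to about 9.5 points.
- The 95% upper limit is below 12 only if the observed disadvantage is below 12 − 9.54 = 2.46 points.

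An observed disadvantage between about 2.5 and 9.5 points is thus not significant, yet does not show non-inferiority. With a 90% interval the cut-off is about 4 points.

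**4. Error rate if a non-significant result were read as non-inferior.** Set the true difference at 12. The test statistic is non-central t with non-centrality 12/SE.
- 35 per arm: P(|T| < 1.995) = 0.303.
- 43 per arm: the corresponding probability is 0.215.

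The normal approximation gives 0.291 and 0.206. A 95% interval rule would accept wrongly 2.5% of the time, and a 90% interval rule 5%. The misreading also becomes more likely to succeed as patients are lost, since 30% at 35 per arm exceeds 21% at 43.

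**The case against.** The strongest reply is that every ingredient is in the document: margin, direction, a two-sided 0.05 level, and a regression interval planned for ODI by name. Only the sentence joining them is absent, and a full protocol or analysis plan that is not shown could contain it. Three stronger readings are tempting, and the text supports none of them.

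- A reader might infer that the planned analysis cannot yield evidence of non-inferiority. It can: the regression interval for the ODI difference is the quantity required.
- A reader might infer that the t-test, or a switch to Mann-Whitney U after a failed Shapiro-Wilk test, will replace the regression for ODI. Section {20a} ties the t-test to symptom rates, and it describes no such switch. The general Mann-Whitney wording includes ODI but does not displace the regression.
- A reader might infer that p>0.05 will be reported as non-inferior. The document says this nowhere, so the 30% and 21% are conditional on a misreading.

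The appeal to an unseen plan does not dispose of the point. The section does not defer the criterion. It states one, under a heading that includes the primary outcome, and that one tests equality. Nor can the missing level be filled in from elsewhere, because the stated alpha and the stated 70 point to different intervals.

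**Conclusion.** The concern holds in this form: the only decision rule stated for the primary outcome is a difference test, and the interval that could decide non-inferiority has no stated level and no comparison with 12. This concerns the trial's main conclusion and should be settled before the 24-month data are analysed.

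Its size depends on the reading. If non-significance were taken as non-inferiority, a true 12-point disadvantage would be accepted about 30% of the time at 35 per arm and 21% at 43. If a 95% interval is used properly, nothing is wrong with the conclusion, but power with 70 evaluable patients is about 71%, not 80%.

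These figures assume SD 20 in both arms and, for power, a true difference of 0. Adjustment for baseline ODI could reduce the residual SD and raise the power; the document gives no correlation from which to say by how much.

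**What to change.** In section {20a}, add a primary decision rule. Decompression is non-inferior if the upper limit of the two-sided 95% confidence interval for the difference (decompression minus fusion) in ODI change from baseline to 24 months is below +12. The interval comes from the already planned linear regression with baseline ODI as a covariate. State that the p<0.05 difference tests and Mann-Whitney U apply to other outcomes, or are supportive only for ODI.

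Then align Sample size {14} with the chosen level:
- keep two-sided 0.05 and the 95% interval, and restate the power at 70 evaluable as about 71% (88 evaluable would be needed for 80%, or 88/0.8 = 110 enrolled at the plan's 20% loss); or
- state one-sided 0.05 and the 90% interval explicitly, in {14} and in {20a}, where the rule above must then name the 90% interval. This is the basis on which 70 reproduces.

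The rule costs one paragraph and no new data. Aligning the sample-size section is also a text change, unless the sponsor chooses to restore 80% power at the 95% level by enrolling more patients.

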## Assignment of interventions: allocation

### Sequence generation {16a}

All participants who meet the inclusion criteria and provide informed consent will be randomly divided into two equal groups (1: 1) according to the applied surgical technique. For the block randomization procedure, stratification based on the severity of lumbar stenosis (Schizas C and D) will be performed. Randomization will be by random permuted blocks of 4 and 6.

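### Two unranked methods cover the primary ODI contrast, and neither is tied to the 12-point margin: fix one ANCOVA whose confidence limit decides non-inferiority

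*Protocol article*

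**What the plan says.** - **Design** (Trial design {8}): "This study is an open-label, non-inferior, multicentre, randomized controlled trial".
- **Primary endpoint** (Outcomes {12}): "the dynamics of ODI parameters at the end of the 24-month follow-up compared to the baseline level", that is, change in ODI over 24 months.
- **Sample size {14}**: "With a non-inferiority margin of δ = 12" and "two-sided α-level of 0.05, power of 80%, and 1:1 allocation ratio, the required sample size is 70 patients". The variability input is described this way: "the standard deviation for the ODI in the fusion group is 20 points".
- **Randomisation** (Sequence generation {16a}): "stratification based on the severity of lumbar stenosis (Schizas C and D) will be performed".
- **Analysis** (Statistical methods {20a}): "Multiple linear regression will be used to measure point estimates and confidence intervals for group differences in the ODI and clinical scale scores", covering baseline to two years. The covariates are not named. The section also calls for Shapiro-Wilk testing of normality, a t-test for normally distributed data in a sentence about symptom rates, and a Mann-Whitney test for continuous variables between groups before and after surgery. Significance is a two-sided p below 0.05.

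**The concern.** A non-inferiority claim needs an interval for the treatment difference, in ODI points, whose unfavourable limit is compared with the margin. The regression can supply that interval. The Mann-Whitney test, as described, supplies a p-value against no difference. A non-significant result there is not evidence of non-inferiority, and a significant one does not say whether the difference exceeds 12 points.

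The ODI is a 0 to 100% score, so it falls under both instructions. Nothing says which governs, and the stated significance rule suits a difference test better than a margin test. In an open-label trial, leaving the deciding method unsettled until the data are seen weakens the primary conclusion.

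Precision is also at stake. The endpoint is worded as change, while baseline ODI and the stratification factor are both available as covariates. Whether the model uses them affects the width of the interval on which the decision rests.

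**Working it through.** **1. Which methods reach the ODI contrast, reading {20a} sentence by sentence**

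| Method | Stated scope | Covers ODI? | Gives a limit to set against 12? |
|---|---|---|---|
| Multiple linear regression | Group differences in ODI and clinical scales | Yes, by name | Yes |
| Mann-Whitney | Continuous variables between groups, pre- and postoperatively | Yes, by scope | No, as a p-value |
| t-test | Symptom rates | Not named | Not applicable |

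Two methods therefore cover the primary contrast. No sentence ranks them or refers to the margin.

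**2. The plan's own sample size**

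Inputs from {14}: margin 12, SD 20, power 80%, 1:1 allocation. A true difference of 0 is assumed, as none is stated.

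n per arm = 2(z₁₋α + z₀.₈)² × 20² / 12²

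- Two-sided 0.05 as stated (one-sided 0.025): 2(1.960 + 0.842)² × 400/144 = 43.6, so 44 per arm and 88 in total.
- One-sided 0.05: 2(1.645 + 0.842)² × 400/144 = 34.3, so 35 per arm and 70 in total.

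The stated 70 is reproduced only at one-sided 0.05. With 35 per arm, SD 20 and two-sided 0.05, power is about 70% (69.7% by noncentral t, 70.9% by normal approximation). This shortfall exists before any question of change scores or covariates arises.

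**3. Change score against ANCOVA**

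Assumptions: 20 is the SD of the ODI score at baseline and at 24 months, in both arms, and r is the correlation between the two. The protocol gives no r, so a range is shown.

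- SD of change = 20√(2(1 − r))
- Residual SD after adjusting for baseline = 20√(1 − r²)
- Variance ratio, change to ANCOVA = 2(1 − r)/(1 − r²) = 2/(1 + r), which exceeds 1 for every r below 1

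Power is by noncentral t with 68 degrees of freedom, 35 per arm, margin 12, true difference 0, two-sided 0.05.

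| r | SD change | SD ANCOVA | Variance ratio | Power, change | Power, ANCOVA |
|---|---|---|---|---|---|
| 0.3 | 23.7 | 19.1 | 1.54 | 55% | 74% |
| 0.4 | 21.9 | 18.3 | 1.43 | 62% | 77% |
| 0.5 | 20.0 | 17.3 | 1.33 | 70% | 82% |
| 0.7 | 15.5 | 14.3 | 1.18 | 89% | 93% |

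Under randomisation both analyses estimate the same difference between arms, so ANCOVA of the 24-month score still answers a question posed as change. The table adjusts for baseline ODI only; the further gain from Schizas grade cannot be computed from the document.

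**4. The SD of 20**

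If 20 is a score SD, the SD of change is above 20 for r below 0.5, equal to 20 at r = 0.5, and below 20 for larger r. If 20 is already the SD of change, it matches the endpoint.

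**The case against.** The strongest reply is that only one sentence names the ODI. It assigns regression with estimates and confidence intervals, which is the right kind of output for non-inferiority, and the Mann-Whitney sentence is generic. A covariate list is commonly left to an analysis plan that is not shown. The recommended ANCOVA is itself a multiple linear regression, so it is compatible with the text.

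Much of this stands, and it rules out several stronger readings:

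- **That the model excludes baseline ODI and Schizas grade.** They are unnamed, not excluded, and the word multiple suggests predictors beyond arm. It does not follow that the planned analysis wastes precision.
- **That three methods compete for the primary contrast.** The t-test is tied to symptom rates. Two methods clearly apply.
- **That the SD used for the sample size is the wrong one.** The protocol does not say which SD it is and gives no correlation. The direction of any error reverses at r = 0.5.
- **That the change score causes the 70% power at r = 0.5.** The SD of change there is exactly the planning SD of 20. The shortfall arises because 70 patients matches one-sided 0.05 and not the stated two-sided 0.05, which is a separate sample-size issue. The powers in the other rows are also computed at two-sided 0.05 and carry the same effect.
- **That ANCOVA always beats any unadjusted analysis.** Against the unadjusted 24-month score, the two are equal at r = 0. The advantage at every r below 1 is over the change score.

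What the reply does not remove is the overlap itself. The Mann-Whitney instruction has no exception for the ODI, and the only stated criterion is a two-sided p-value with no reference to the margin. That is a conflict between stated rules, not merely missing detail.

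**Conclusion.** The point holds as a conflict in the stated analysis rules and as an improvement available at no cost. Section {20a} leaves two unranked methods on the primary contrast, only one of which can address the 12-point margin, and states no margin-based decision rule.

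Naming a baseline-adjusted model would settle this. Compared with a change-score analysis it would raise power by about 19 percentage points at r = 0.3, 12 at r = 0.5 and 4 at r = 0.7. Those figures rest on a score SD of 20 at both times and in both arms, 35 evaluable patients per arm, no true difference, and the r shown. The ordering does not depend on r, as long as it is below 1. The meaning of the SD of 20 is an ambiguity to clear up, not a demonstrated error.

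**What to change.** - Name one primary analysis: linear ANCOVA of 24-month ODI on arm, baseline ODI and Schizas grade (C or D). Centre may be added.
- State the decision rule: non-inferiority is declared if the limit of the two-sided 95% confidence interval for the adjusted difference that is unfavourable to decompression lies inside 12 points.
- State that neither the Mann-Whitney test nor a choice of method driven by Shapiro-Wilk applies to the primary endpoint.
- In Sample size {14}, say whether 20 is the SD of the ODI score or of its change. Resolve the one-sided against two-sided alpha separately; adjustment may recover power but does not correct that statement.

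The cost is wording only, in the protocol or analysis plan, and it should be settled before outcome data are seen by arm. Table 2 already schedules ODI before surgery, and Schizas grade is needed for eligibility and randomisation, so no new data are required.
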